#### Secondary outcomes

A number of secondary outcome measures will be collected to help shape future trials in terms of assessing potential primary outcome measures and monitoring safety end points.

Intraoperative cell salvage volume (as a proxy for blood loss).Intraoperative urine output during each surgical phase.Mean arterial blood pressure during each surgical phase.Requirement for and mean vasopressor and/or inotrope infusion rate during each surgical phase.Volume or mass of de novo packed red blood cells and other clotting products during surgery and on the ICU (within first 24 hours, 72 hours and 1 week).Incidence of AKI as defined by the Acute Kidney Injury Network stage 1 criteria (a 50% increase in serum creatinine from baseline or less than 0.5 mL/kg/hours urine output for 6–12 hours post transplant) within 24 hours, 72 hours, 1 week.Incidence of postoperative RRT at 24 hours, 72 hours, 1 and 2 weeks postoperatively.Incidence of new or worsened CKD at 30 and 90 days.Mortality, early allograft dysfunction, graft loss and liver graft function at 30 and 90 days.Patient recorded outcome measures (PROM) preoperatively and at 90 days postoperatively;Liver Disease Quality of Life questionnaire.^28^EuroQOL-5D-5L questionnaire.^29^

Major safety outcomes will include:

Unexpected or resistant bradycardia,.Abnormal QTc interval (460 ms in men, 470 ms in women) or associated ventricular arrhythmia or Torsades de Pointes.Unexpected or resistant hypoglycaemia (blood sugar <4 mmol/L).Potential allergic or anaphylactic reaction to any medication.Any report of an abnormal response to codeine or morphine.Development of venous or arterial thrombosis.Cardiac event including acute coronary syndrome, new heart failure, arrhythmia or resuscitated cardiac arrest.

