## Introduction

Liver transplantation is a potentially life transforming intervention with excellent outcomes (1-year and 5-year survival of 94% and 84%, respectively).^1^ It is, however, a major operation in patients with multiple comorbidities and is associated with a 3% perioperative mortality rate and 70% complication rate. Intraoperative haemorrhage is serious and commonly occurs during mobilisation of the diseased liver, exacerbated by coagulopathy and abnormal vasculature due to portal hypertension. Bleeding can cause hypotension, reduced perfusion of the transplanted graft and increased incidence of acute kidney injury (AKI). Blood loss and transfusion are associated with increased morbidity, mortality and cost of transplantation and can have a long-term detrimental effect on patient well-being and quality of life.^2–4^

Octreotide is a synthetic analogue of somatostatin with an excellent safety profile^5^ that may improve renal outcomes, reduce perioperative bleeding and increase exogenous vasopressor sensitivity during liver transplantation. AKI following liver transplantation occurs in 25%–60% of patients with normal renal function prior to surgery, with half of these patients requiring renal replacement therapy (RRT) after surgery.^6 7^ The need for post-transplant RRT increases the length of hospital stay and the risk of early allograft dysfunction, chronic kidney disease (CKD) and mortality.^8 9^ Risk factors for renal dysfunction following transplantation include intraoperative hypotension, lower quality donor grafts, hepatic ischaemia-reperfusion injury, blood transfusion and preoperative renal disease.^10 11^ Octreotide has been shown to enhance renal blood flow, glomerular filtration and urine output in decompensated liver cirrhosis,^12^ hepatorenal syndrome^13^ and may also reduce the incidence of post-transplant renal injury.^14 15^

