Key inclusion and exclusion criteria	Ages eligible for study: ≥18 years Sexes eligible for study: both Accepts healthy volunteers: no
	Inclusion criteria: adults aged 18 years and over undergoing primary liver transplantation of a whole or partial liver graft from a cardiac or brain dead donor
	Exclusion criteria: previous solid organ transplant, acute liver failure, fulminant hepatic failure, patients receiving a living donor liver graft, patients currently admitted to ICU prior to transplantation, requirement of haemodialysis or continuous veno-venous haemofiltration (CVVHF) preoperatively, known allergy or adverse reaction to octreotide, preoperative decision to use intra-operative CVVHF, a positive pregnancy test.
Study type	Interventional
	Allocation: patients will be randomised in a 2:1 ratio to either octreotide or placebo groups. Stratified randomisation of patients by source of liver graft (brain death or cardiac death). Masking: quadruple (participant, care provider, investigator, outcomes assessor)
	Primary purpose: feasibility
	Phase II
Date of first enrolment	July 2021
Target sample size	30
Recruitment status	Pending recruitment
Primary outcome(s)	Trial feasibility
Key secondary outcomes	Incidence of acute kidney injury Postoperative incidence of a new requirement for renal replacement therapy Incidence of new chronic kidney disease or deterioration of chronic kidney disease Incidence of early allograft dysfunction Patient mortality Intra-operative red blood cell salvage Volume of packed red blood cell transfusion administered Incidence of adverse events secondary to study drug infusion PROMs data

ICU, intensive care unit; PROMs, patient recorded outcome measures.

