### Sample size

Thirty patients will be recruited from two sites, with 20 in the study drug (octreotide) arm and 10 in the placebo. This sample will allow us to demonstrate the feasibility of conducting a full-scale randomised trial. This study is not powered to detect differences in treatment effect but will obtain estimates of an effect and its variance.^30^ This sample size will allow us to estimate patient consent rate with a 95% CI of ± 10% (based on 100 participants approached). The secondary outcome data will provide the required information for a sample size calculation for the primary end point of a subsequent trial.^31^ Survival to discharge is above 96% for both study sites and hence it is likely that the ninety day follow data collection will be achieved for the majority of patients.

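### The 72-hour and 1-week transfusion totals stop counting when the patient leaves the ICU

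*Protocol article*

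**What the plan says.** All references are to the protocol article.

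- **Outcomes, Secondary outcomes.** The transfusion outcome is the amount of "packed red blood cells and other clotting products during surgery and on the ICU (within first 24 hours, 72 hours and 1 week"). It sets two limits at once: a place (theatre or ICU) and a time (up to 1 week).
- **Same section, purpose.** The secondary outcomes are there to "help shape future trials in terms of assessing potential primary outcome measures and monitoring safety end points".
- **Sample size.** "The secondary outcome data will provide the required information for a sample size calculation for the primary end point of a subsequent trial".
- **Trial design, Table 1.** The registration summary lists "Volume of packed red blood cell transfusion administered", with neither place nor window.
- **Secondary outcomes, renal items.** AKI is defined by "a 50% increase in serum creatinine from baseline or less than 0.5 mL/kg/hours urine output for 6–12 hours post transplant", as incidence within 24 hours, 72 hours and 1 week. The next item is "Incidence of postoperative RRT at 24 hours, 72 hours, 1 and 2 weeks postoperatively".

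**The concern.** A total to 72 hours or 1 week should observe every patient for that long. Here the place limit overrides the time limit: a patient who goes to the ward on day 2 contributes two postoperative days to a seven-day outcome, and a patient who goes on day 5 contributes five. ICU discharge follows randomisation and could depend on treatment. If the arms differed in ICU stay, the counted units would differ even with identical bleeding, in whichever direction the stays differed.

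Site matters too. Under Study interventions, care otherwise follows each centre's standard protocol. Under Randomisation, the only stratification factor is graft source. Under Sensitivity and other planned analyses, the impact of hospital site is to be assessed. Any difference between centres in ICU discharge practice would therefore enter that comparison and inflate the overall variance.

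At stake are the mean, the variance and the apparent effect for a candidate main-trial endpoint.

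**Working it through.** **1. The plan's own figure.** The only computed precision in the article is a 95% CI of ±10% for the consent rate with 100 patients approached. At a rate of 50%: 1.96 × √(0.5 × 0.5 / 100) = 0.098, so it reproduces. It does not depend on the transfusion definition.

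**2. Inputs for the transfusion point.** Place and windows come from Secondary outcomes. The article gives no ICU stay and no ward transfusion rate, so these are assumptions:
- postoperative rate *r* = 0.25 to 0.5 units per day, constant over 7 days and equal in both arms;
- one ICU stay of 4 days in one arm and 2 days in the other.

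**3. Formula.** For a window of *W* days and an ICU stay of *D* days, units counted = *r* × min(*D*, *W*) and units given = *r* × *W*. The true difference between arms is zero.

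| Window | Units given, each arm | Counted, 4-day stay | Counted, 2-day stay | Spurious difference |
|---|---|---|---|---|
| 24 hours | 0.25–0.5 | 0.25–0.5 | 0.25–0.5 | 0 |
| 72 hours | 0.75–1.5 | 0.75–1.5 | 0.5–1.0 | 0.25–0.5 |
| 1 week | 1.75–3.5 | 1.0–2.0 | 0.5–1.0 | 0.5–1.0 |

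For scale, the section on previous clinical studies cites a non-significant reduction of 2.3 units in a retrospective cohort. The spurious 1-week difference is 0.5/2.3 = 22% to 1.0/2.3 = 43% of that.

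**4. Equal stays.** With 3 ICU days in both arms there is no spurious difference, but 1 − 3/7 = 57% of the postoperative units in the week go uncounted at a constant rate. The mean carried forward is too low.

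**5. The AKI rule.** The text has no RRT criterion. Because the outcome is incidence within a window, a patient who meets the creatinine or urine rule before RRT stays counted; a later fall in creatinine under dialysis does not undo it. Only a patient who starts RRT without ever meeting either rule is missed. The Introduction says AKI "occurs in 25%–60% of patients with normal renal function prior to surgery, with half of these patients requiring renal replacement therapy (RRT) after surgery". If a share *f* of those RRT patients were missed, observed AKI = AKI × (1 − 0.5*f*). At an assumed *f* = 0.1 this gives 0.25 × 0.95 = 23.8% or 0.60 × 0.95 = 57%. The documents give no value for *f*.

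**The case against.** **A perioperative measure is a defensible choice.** Under Study interventions, the infusion ends on transfer to the ICU at the latest, so a theatre-plus-ICU count stays close to the exposure. The intraoperative part is untouched by ICU stay, and so is the 24-hour total for anyone still in the ICU at 24 hours. This stands, and it is why those subtotals should be kept. It does not explain a 1-week total whose observed length varies from patient to patient.

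**The size is assumed.** This also stands. Nothing in the article shows that octreotide changes ICU stay or that many units are given on the ward. If transfusion is concentrated early, a constant rate overstates the loss.

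**Table 1 might be read as contradicting the outcome definition.** It does not. It is a registration summary that also leaves out the windows, the clotting products and the AKI criteria. Its silence on place is condensation.

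**A reader might infer that the AKI rule loses the worst renal cases, up to half of them.** The documents do not support that. The Introduction's rates imply 12.5% to 30% of patients on RRT (0.25 × 0.5 and 0.60 × 0.5), or 3.75 to 9 of 30, but those patients are already AKI cases in that figure, which describes patients whose renal function was normal before surgery. Calling them all missed means setting *f* = 1. RRT is recorded over every AKI window, so a combined outcome can be built from data already collected, and the analysis plan may settle the rule.

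**Conclusion.** The transfusion point holds. As worded, ward units inside the 72-hour and 1-week windows are left out, and the observed window depends on a post-randomisation event. The illustrated 0.5 to 1.0 units rests entirely on the assumed rate and stays; the true size and direction are unknown.

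Two stronger readings should be resisted. ICU stay is not itself a listed outcome of this trial, so the argument is only that it follows randomisation. And the share of the week spent in the ICU is a share of time; it equals the share of units only if the rate is constant.

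The consequence is confined to a secondary outcome in a feasibility study with no formal tests. It matters because these data feed the design of the next trial, and units that are never collected cannot be recovered in analysis. The AKI item is a minor clarification.

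**What to change.** **Transfusion.** Count all red cells and clotting products from the start of surgery to 24 hours, 72 hours and 7 days, wherever in hospital they are given, and report theatre and ICU amounts as subtotals. The perioperative measure is then still available, and the totals no longer stop at ICU discharge. A hospital discharge before day 7 would still end the count, but that cannot come earlier than ICU discharge, so no patient is observed for less time than now.

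**Cost.** A change of outcome wording and slightly more extraction for ward transfusions. The Data collection section describes the in-hospital data as part of routine care, though it does not name the transfusion records.

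**AKI.** Add one sentence stating whether a patient who starts RRT within the window without first meeting the creatinine or urine rule counts as AKI. No new data are needed.

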## Abstract

**Introduction:**

Liver transplantation is a complex operation that can provide significant improvements in quality of life and survival to the recipients. However, serious complications are common and include major haemorrhage, hypotension and renal failure. Blood transfusion and the development of acute kidney injury lead to both short-term and long-term poor patient outcomes, including an increased risk of death, graft failure, length of stay and reduced quality of life. Octreotide may reduce the incidence of renal dysfunction, perioperative haemorrhage and enhance intraoperative blood pressure. However, octreotide does have risks, including resistant bradycardia, hyperglycaemia and hypoglycaemia and QT prolongation. Hence, a randomised controlled trial of octreotide during liver transplantation is needed to determine the cost-efficacy and safety of its use; this study represents a feasibility study prior to this trial.

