#### Risks

Octreotide is not currently licensed for use in liver transplantation. Common risks of octreotide include changes in blood sugar levels, heart rate and rhythm. The side effect profile of octreotide during liver transplantation is unknown. The studies to date did not compare safety or adverse events between the octreotide and placebo arms,^15^ have not been fully published^25^ or did not assess adverse events.^24^

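### The safety outcomes cover low but not high glucose, although hyperglycaemia is a named risk, and the QTc cut-off as worded does not exclude prolongation present before the infusion

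*Protocol article*

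**What the plan says.** The introduction paragraph of the Abstract states that "octreotide does have risks, including resistant bradycardia, hyperglycaemia and hypoglycaemia and QT prolongation". The Risks section gives the glucose risk without a direction: "Common risks of octreotide include changes in blood sugar levels, heart rate and rhythm". It adds that "The side effect profile of octreotide during liver transplantation is unknown", and that the earlier studies did not compare harms between arms, were not fully published or did not assess adverse events.

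Under Outcomes, Secondary outcomes, the measures are collected "to help shape future trials in terms of assessing potential primary outcome measures and monitoring safety end points". The list of major safety outcomes there has one glucose item, "Unexpected or resistant hypoglycaemia (blood sugar <4 mmol/L", and defines the ECG item as "Abnormal QTc interval (460 ms in men, 470 ms in women) or associated ventricular arrhythmia or Torsades de Pointes".

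Three other places bear on the point:

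- Table 1 names, as a key secondary outcome, the incidence of adverse events attributed to the study infusion.
- The Adverse events section sends all adverse events to the medical records initially, and says that serious events within 90 days go into the eCRF.
- Statistical methods lists the variables for baseline comparability, without QTc or glucose. Its Secondary outcomes subsection plans between-group differences with 95% confidence intervals and no tests.

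**The concern.** The study is meant to supply safety information that the protocol says does not yet exist in this setting, and its rationale sets harm against efficacy and cost. Two of the definitions do not fit that purpose.

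First, of the four risks named in the Abstract, three have a matching safety outcome and hyperglycaemia has none. A later trial would inherit a by-arm figure for low glucose and no counterpart for high glucose.

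Second, the QTc item carries no new-onset, change or timing condition. A candidate already above the cut-off before induction would meet the definition as written. The reported rate could then mix pre-existing abnormality with any effect of the drug, in arms of only 20 and 10.

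**Working it through.** The plan gives no rate, threshold for high glucose or precision figure for either outcome, so there is no figure of its own to reproduce on this point. The check is a comparison of texts, then an illustration with assumed values.

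**Step 1: named risks against listed outcomes**

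| Risk named in the Abstract | Item in the major safety list |
|---|---|
| Bradycardia | yes |
| Hypoglycaemia | yes, with a threshold |
| QT prolongation | yes, with a cut-off |
| Hyperglycaemia | none |

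Neither Table 1 nor the primary or secondary outcome lists name high glucose.

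**Step 2: baseline conditions in the same section**

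The AKI outcome is a rise in creatinine relative to baseline. The CKD outcome is "Incidence of new or worsened CKD at 30 and 90 days". The cardiac item reads "Cardiac event including acute coronary syndrome, new heart failure, arrhythmia or resuscitated cardiac arrest", so heart failure must be new. The QTc item alone has an absolute level and no such condition. The section therefore uses baseline conditions elsewhere, and the QTc wording does not exclude prevalent cases.

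**Step 3: what prevalent QTc cases would do**

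Inputs from the Sample size section: 20 octreotide and 10 placebo patients. Assumed, because the documents give no figure: a share b above the cut-off before infusion, equal in expectation in both arms, and new-onset rates p of 20% (octreotide) and 5% (placebo) among the rest.

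Observed rate per arm = b + (1 − b) × p. Observed difference = (1 − b) × (true difference).

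For b = 30%: 0.30 + 0.70 × 0.20 = 44.0%, and 0.30 + 0.70 × 0.05 = 33.5%.

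| Assumed b | Octreotide | Placebo | Difference | Ratio |
|---|---|---|---|---|
| 0% | 20.0% | 5.0% | 15.0 points | 4.0 |
| 10% | 28.0% | 14.5% | 13.5 points | 1.93 |
| 30% | 44.0% | 33.5% | 10.5 points | 1.31 |
| 50% | 60.0% | 52.5% | 7.5 points | 1.14 |

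**Step 4: noise at b = 30%**

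- Literal definition: SE = √(0.44 × 0.56/20 + 0.335 × 0.665/10) = 18.6 points, around a difference of 10.5.
- New onset among patients below the cut-off at baseline (14 and 7 expected): SE = √(0.20 × 0.80/14 + 0.05 × 0.95/7) = 13.5 points, around a difference of 15.0.
- New onset among all randomised patients (0.70 × 20% = 14% and 0.70 × 5% = 3.5%): SE = √(0.14 × 0.86/20 + 0.035 × 0.965/10) = 9.7 points, around a difference of 10.5.

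So a new-onset rule reduces the noise with either denominator. It restores 20% versus 5% only when the denominator is the patients at risk.

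**Step 5: chance imbalance**

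With binomial counts X in 20 and Y in 10 at the same b, the exact probability that |X/20 − Y/10| is at least 15 points, with no drug effect, is 27% at b = 10%, 42% at b = 20% and 48% at b = 30%.

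**The case against.** The strongest reply is that the gap is narrower than it looks. The safety list is introduced in open-ended terms and covers major outcomes. Serious hyperglycaemia would be reported as a serious adverse event. The general adverse event outcome in Table 1 is not limited to serious events or to one direction of glucose change. ECG timing and event rules are details that an article may leave to the full protocol or the SAP. The placebo arm protects the comparison. All of this stands as a limit on the point.

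It does not remove it. The general outcome depends on someone attributing the event to the infusion and sets no glucose definition, so it does not replace a comparison of measured values by arm. Choosing which harms to list is a matter for the protocol, and this list gives one direction of glucose change a threshold and omits the other.

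Three stronger readings are tempting and are not supported:

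- A reader might infer that hyperglycaemia cannot be estimated at all, or that only serious events enter the eCRF. The text says serious events will be entered and does not say that others will not. The eCRF fields are not shown.
- A reader might infer that patients with prolonged QTc before infusion will be counted as events. The protocol does not say so; its wording merely fails to exclude them. The baseline list serves group comparability, so the absence of QTc there does not show that no pre-infusion ECG is used.
- A reader might infer bias against one arm. Randomisation spreads prevalent cases equally in expectation, and the effects in Steps 3 to 5 are inflation, dilution and noise.

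**Conclusion.** The point holds in limited form. For glucose, the plan names a harm in its Abstract and lists no outcome that compares it by arm; what is exposed is mainly hyperglycaemia that is neither serious nor attributed to the drug. For QTc, the literal definition admits prolongation present before the infusion, which would inflate both rates, dilute the difference by the factor (1 − b) and add variability at 20 versus 10.

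The size of the QTc effect is unknown. The figures above rest on assumed baseline shares and assumed new-onset rates and show only the mechanism. The glucose half rests on the text alone and is the firmer of the two. These are secondary safety outcomes in a feasibility study without tests, so the consequence is a weaker safety basis for the later trial. No primary conclusion is affected. The correction is worth making because it is cheap.

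**What to change.** - **Glucose:** add hyperglycaemia to the major safety outcomes with one prespecified definition used at both sites, and summarise the lowest and highest glucose by arm over a stated window. A definition taken from each site's laboratory would make the outcome depend on site. The clinical threshold is for the investigators to set.
- **QTc:** count an event only when it is new relative to the last pre-infusion ECG, and state the ECG window and whether the denominator is all patients or those below the cut-off at baseline. Report change from that ECG by arm, and add QTc to the baseline table.

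The cost is a few eCRF fields. The Data collection section says that the required in-hospital data come from routine care, so most values should already exist. Where a pre-infusion ECG is not routine, one extra reading is needed. If the full protocol or SAP already contains these rules, it is enough to align the outcome wording with them.

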### Data collection

Data will be collected on trial-specific electronic CRFs (eCRFs) and anonymised data collated on a secure central trial database (MACRO, Elsevier, Amsterdam, Netherlands) on a server in University College London (UCL). Physical trial material will be stored locally at each study site in a secure setting. A trial-specific data management standard operating procedure will contain details of the software to be used for the database, the process of database design, data entry, data quality checks, data queries, data security and database lock. At the end of the trial, all essential documentation will be archived securely for a minimum of 20 years from the declaration of the end of the trial.

All in-hospital data required for the study is part of routine medical care and as such is expected to have a high rate of completeness. Out-of-hospital data is similarly part of routine medical care. The completeness of study-specific PROM questionnaires performed before and after transplantation will be maximised through reminders by telephone and during clinic appointments.

Data will be analysed for completeness and accuracy through a check of 10% of patient records against the source data.

Third party data access will be assessed on a case-by-case basis by the Trial Management Group (TMG), approved by the TSC and limited specific anonymised data will be released, as appropriate. Patients will be consented for further analysis of anonymised data.

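### The hypoglycaemia safety outcome counts a blood sugar below 4 mmol/L only if it is also judged unexpected or resistant, so its reported incidence can fall below the true one

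*Protocol article*

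**What the plan says.** Under Outcomes, Secondary outcomes, the protocol article gives a list of major safety outcomes. Three of its items matter here:

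- Hypoglycaemia: "Unexpected or resistant hypoglycaemia (blood sugar <4 mmol/L"), a numeric cut-off with a qualifier in front of it.
- Bradycardia: "Unexpected or resistant bradycardia", the same qualifier with no heart-rate value.
- QTc: "Abnormal QTc interval (460 ms in men, 470 ms in women"), numeric limits with no such qualifier.

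The same section says that the secondary outcomes serve the purpose of "assessing potential primary outcome measures and monitoring safety end points". The Risks section of the Introduction states: "Common risks of octreotide include changes in blood sugar levels, heart rate and rhythm". It adds: "The side effect profile of octreotide during liver transplantation is unknown". The abstract says that "octreotide does have risks, including resistant bradycardia, hyperglycaemia and hypoglycaemia and QT prolongation". On data sources, Data collection states: "All in-hospital data required for the study is part of routine medical care".

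The Adverse events section sends all adverse events to the medical records first. It states eCRF entry, and later analysis and publication, for serious adverse events. Table 1 lists among the key secondary outcomes the incidence of adverse events secondary to the study drug infusion.

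**The concern.** A glucose below 4 mmol/L is a plain yes-or-no measurement. Adding a condition that the episode be unexpected or resistant turns it into a judgement, and the article defines neither word. An effect that the protocol itself calls common can readily be regarded as expected. If it then responds to treatment it is not resistant either, and it drops out of the count.

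At stake is the usefulness of the safety data. The protocol presents the side effect profile in this setting as an open question and intends these outcomes to inform a later trial. A filtered count does not estimate how often hypoglycaemia occurs on octreotide during transplantation. It also depends on how assessors at two centres understand two undefined words. A low or zero count could then be read as reassurance that the data do not give.

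**Working it through.** **No figure to reproduce.** The article states no expected incidence, precision or power for hypoglycaemia or bradycardia. The check is of the wording first, then an illustration on assumed values.

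**Step 1: what is counted.** Let A be the patients with any blood sugar below 4 mmol/L, and B the patients with at least one such episode judged unexpected or resistant. The outcome counts B, and B is a subset of A. The two counts agree only if every patient in A qualifies. Defining the two words in an analysis plan would make B reproducible but would not turn it into A.

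**Step 2: whether another item recovers the patients in A but not in B.**

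| Other route | Recovers non-serious hypoglycaemia? | Recovers non-resistant bradycardia? |
|---|---|---|
| Serious adverse events (Adverse events section) | No, serious events only | No, serious events only |
| Medical records (Adverse events section) | Recorded there, but eCRF entry and publication are stated only for serious events | Same |
| Adverse events secondary to study drug (Table 1) | Only if judged drug-related | Only if judged drug-related |
| Arrhythmia under cardiac events (Secondary outcomes) | No | Possibly, and without the qualifier |

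Non-serious hypoglycaemia has no unfiltered route. Bradycardia may have one.

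**Step 3: illustration of size.** Inputs: 20 octreotide patients (Sample size section). Assumed, because the documents give neither: p, the true share of patients with any episode, and f, the share of those patients who have one judged unexpected or resistant.

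Counted incidence = p × f. Expected count = 20 × p × f. Probability of no counted patient = (1 − p × f)^20.

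| p (assumed) | f (assumed) | Expected count | Probability of 0 of 20 |
|---|---|---|---|
| 10% | 1 | 2 | 0.90^20 = 12.2% |
| 10% | 0.5 | 1 | 0.95^20 = 35.8% |
| 10% | 0.25 | 0.5 | 0.975^20 = 60.3% |
| 20% | 1 | 4 | 0.80^20 = 1.2% |
| 20% | 0.5 | 2 | 0.90^20 = 12.2% |
| 20% | 0.25 | 1 | 0.95^20 = 35.8% |
| 40% | 1 | 8 | 0.60^20, below 0.1% |
| 40% | 0.5 | 4 | 0.80^20 = 1.2% |
| 40% | 0.25 | 2 | 0.90^20 = 12.2% |

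Exact 95% intervals for n = 20: 4/20 gives 5.7% to 43.7%, 2/20 gives 1.2% to 31.7%, and 1/20 gives 0.1% to 24.9%.

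**Step 4: effect on the comparison.** If f is the same in both arms, the risk difference becomes f × (p octreotide − p placebo). For assumed rates of 20% and 10%, the 10-point difference becomes 0.5 × 10 = 5 points or 0.25 × 10 = 2.5 points.

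**The case against.** The strongest reply is that the restriction is deliberate. The list is headed as major safety outcomes and is introduced as inclusive, not exhaustive, so it may be meant to catch important events and not every excursion. That is a fair reading and explains the qualifier. It does not supply an incidence for an effect the protocol says is unknown in this setting. The restricted count can be kept as a subset, so nothing the authors wanted is lost.

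Second, *unexpected* may mean unexpected for that patient at that point in surgery. Because staff and assessors are blinded, they cannot dismiss an episode on the ground that the patient is known to be on octreotide. This stands in part: the word has more than one reading, and blinding protects the comparison. On either reading, however, the word removes some episodes below the cut-off.

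Third, a condensed article may leave definitions to the full protocol or analysis plan. That is accepted, and the absent definitions alone would not be a finding. The finding is the stated condition, which would remain once the words were defined.

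Fourth, a reader might infer that bradycardia is undercounted in the same way. The documents do not support this as firmly. The abstract names the hazard itself as resistant bradycardia, so the outcome matches the named risk, and arrhythmia appears without a qualifier under cardiac events.

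Fifth, the consequence is limited. None of the six feasibility targets uses these items, no formal tests are planned and there are no statistical stopping rules. All of this stands.

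**Conclusion.** The point holds for non-serious hypoglycaemia. The outcome as worded counts a judgement-dependent subset of patients with a reading below 4 mmol/L, and no other item reliably recovers the rest. The reported incidence is below the true one whenever any patient with such a reading is judged not to qualify.

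The size cannot be derived from the documents. The values of p and f above are assumptions and show only that, with 20 patients, a modest filter could make a zero count plausible. That glucose is charted routinely is inferred from the general statement in Data collection, which does not name it.

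Two stronger readings should not be drawn. One is that the filter favours octreotide: with blinded assessment, the likely effect is undercounting in both arms and a diluted difference, not a clear bias towards one. The other is that bradycardia certainly goes uncounted: it may be captured as arrhythmia, and what is needed there is a clarification. This is an inexpensive improvement to the safety data and does not threaten the feasibility conclusions.

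**What to change.** **Hypoglycaemia.** Report by arm the number (%) of patients with any recorded blood sugar below 4 mmol/L after the start of the study infusion, using the protocol's own cut-off. Report the unexpected or resistant episodes as a subset of that count.

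**Bradycardia.** State whether non-resistant bradycardia is counted under arrhythmia. If it is not, count it against one heart-rate cut-off that the investigators pre-specify for both sites.

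**Cost.** A change of outcome wording and a CRF field for glucose, with one more for heart rate if needed, filled from in-hospital data that the article describes as routine. No treatment or visit changes. The drawback is that ordinary perioperative episodes are counted too, and the placebo arm of 10 gives only an imprecise background rate: 5 of 10, for example, has an exact 95% interval of about 19% to 81%. The between-arm difference should be presented with that imprecision in view.
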